### Objectives

The main goal of the present study is to evaluate whether the use of the app-based intervention helps to decrease symptoms of social anxiety disorder and has positive effects on mental health. There will be two experimental treatment conditions: App-based CT (APP) and app-based CT plus 8 therapist-guided video-delivered therapy sessions (TG-APP). Both will be compared to a wait-list control group (WLC). The therapists will be trained in Cognitive Therapy based on the model of Clark and Wells [4], which has been proven to be effective in face-to-face therapy [5] and in ICBT [15]. In a randomized controlled trial (RCT), the following hypotheses will be tested:Hypothesis 1a: In the APP and TG-APP condition, SAD-related symptoms, as measured by the LSAS, will decrease significantly more from baseline to post-treatment than in the WLC condition.Hypothesis 1b: The TG-APP condition results in a significantly greater reduction in SAD-related symptoms, as measured by the LSAS, than the APP and the WLC conditions, from baseline to post-treatment.Hypothesis 1c: In the APP and the TG-APP condition, there will be no significant deterioration of SAD-related symptoms, as measured by the LSAS, from post-treatment to follow-up.Hypothesis 2a: In the APP and TG-APP conditions, significant improvements in secondary outcome variables, including social phobic cognitions, depression symptoms, general psychological distress, psychological impairment, quality of life, and interpersonal pleasure, are achieved from baseline to post-treatment compared to the WLC condition.Hypothesis 2b: In the TG-APP condition, improvements in secondary outcome variables from baseline to post-treatment will be significantly larger than in the APP condition.Hypothesis 2c: In the APP and TG-APP condition, there will be no significant deterioration in secondary outcome variables from post-treatment to follow-up.Hypothesis 3: Individual learning styles contribute significantly to predicting success in both treatment conditions.Hypothesis 4: The increase in social approach behavior will mediate the effect of the TG-APP versus APP condition.

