We based our power analysis on an iterative simulation of increasing sample sizes with starting values of *n* = 30 for the control condition and *n* = 50 for each of the treatment conditions, increasing stepwise by one participant per condition. The variance of the random intercepts and residual variance was set to 0.5 respectively [24]. Because missing values due to the dropout of participants were planned to be imputed by the jump to reference method (J2R) [25], the reference being the control condition, we reduced our expected effected sizes by multiplying them with the term (1—dropout-rate). Given a dropout rate of 26% at post-treatment evaluation in the study by Stolz et al. [16] and a pooled post-treatment dropout rate of 26.2% in a meta-analysis of studies using smartphone apps by Torous et al. [26], we chose a conservative estimate of 30% post-treatment dropout for the APP condition and multiplied the expected effect size of 0.5 by 0.7, equaling to *d* = 0.35. For the TG-APP condition, we expected a lower post-treatment dropout rate of 20% due to the additional guidance by a therapist and multiplied the expected effect size of 0.8 by 0.8, equaling to *d* = 0.64. Based on 500 simulations of the linear mixed model fitted with the expected effect sizes, we obtained the power of finding a statistically significant interaction of group × time based on a likelihood ratio test, compared to finding only main effects, and the 95% confidence interval for this estimate, for increasing sample sizes. We located the minimum sample size in our results after which the lower bound of the 95% confidence interval did not fall below 80% power, given *α* = 0.05. This condition was met at *n* = 41 for the control group and *n* = 61 for both treatment conditions (power estimate = 84%, 95% confidence interval = 80.0, 87.0). In addition to our study purposes, the app provider intends to use the results of the pilot study and the main study for the licensing process of the app as a digital health product. For this licensing process, a separate statistical analysis will be conducted comparing only the APP condition with the WLC condition, using a *t*-test for statistical analysis. A corresponding additional sample size calculation revealed the need to recruit 43 subjects in the wait-list control group (WLC). To establish conformity across the planned analyses we adjusted the number of participants for WLC upward to *n* = 43, resulting in a total sample size of *N* =165 (see also Fig. 1).

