#### Primary analysis

For our primary analysis, we plan to fit a linear mixed model with random intercepts for participants in the R package lme4 [61]. We take the *z*-standardized values of the Liebowitz Social Anxiety Scale (LSAS) as the outcome variable, and time and treatment condition as categorical predictors, for which we specify an interaction term. The estimated effects of the predictor variables indicate the change in LSAS from baseline at week 0, which we choose as the reference category, to post-treatment.

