#### Secondary analyses

As secondary analyses, we will evaluate treatment effects (from baseline to post-treatment, as described in hypothesis 2a and from post-treatment to follow-up, as described in hypothesis 2c) on quality of life, as measured by the WHO-QOL-BREF, interpersonal pleasure, as measured by the ACIPS, further SAD-related symptoms, as measured by the SPIN and the CGI, social phobic cognitions, as measured by the SPK, symptoms of depression, as measured by the BDI-FS and the QIDS-C, general psychological distress, as measured by the BSI, and limitations in everyday life, as measured by the PDI. We will also assess adverse effects measured by the self-developed adverse effect scale. Moreover, we will compare posttreatment LSAS scores with scores at follow-up, as stated in hypothesis 1c, using the linear mixed model described earlier.

To control for moderating effects on decreases in social anxiety symptoms, as indicated in hypothesis 3, we include the scores of the individual learning style, as measured by Kolb’s LSI and experienced pain in social situations, as measured by the SPQ-5, as predictors in the model and specify three-way interactions with treatment conditions and time for all these factors. We will conduct a similar analysis to test whether social approach behavior measured by the SPWSS has a mediating effect on social anxiety symptoms, as we hypothesized in hypothesis 4. We will test all interactions by comparing the full to a reduced model without the respective interaction term via likelihood ratio tests (LRTs) [62] and remove all non-significant interactions from the final model.

To evaluate effects between two conditions at a given time, e.g., between the APP and TG-APP conditions at post-treatment, as indicated in hypothesis 1b and 2b, we will calculate the statistical significance of pairwise differences in LSAS based on the linear mixed model using the R package “emmeans” [63].

We will fit all measures as outcome variables in linear mixed models including the same predictors as in the primary analysis and add the average weekly time participants spent using the app and the number of behavioral experiments conducted as additional explanatory predictors.

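### H1a is read from change and H1b from post-treatment level, and neither contrast uses baseline LSAS efficiently: about 25% of the contrast variance is forgone at the planned correlation

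*Protocol article*

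**What the plan says.** The Objectives section words H1b as a comparison of reductions: "The TG-APP condition results in a significantly greater reduction in SAD-related symptoms", from baseline to post-treatment, against both APP and WLC. H1a is also worded as a larger decrease from baseline.

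The Primary analysis section specifies a linear mixed model with a random intercept per participant and with time, condition and their interaction as categorical predictors. Baseline LSAS is one of the outcome occasions, so each arm has its own baseline mean. The effects are read as change: "The estimated effects of the predictor variables indicate the change in LSAS from baseline at week 0".

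The Secondary analyses section handles H1b and H2b differently. It compares two conditions at a given time, with APP against TG-APP at post-treatment as the example, and states: "we will calculate the statistical significance of pairwise differences in LSAS based on the linear mixed model using the R package" emmeans.

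The Design and sample size section powers only the interaction: "we obtained the power of finding a statistically significant interaction of group × time based on a likelihood ratio test". For that simulation, "The variance of the random intercepts and residual variance was set to 0.5 respectively".

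**The concern.** A hypothesis about reduction is to be tested by a difference in level. With free baseline means, the post-treatment difference between two arms and their difference in change are separate quantities, and they differ by exactly the baseline difference observed in the sample. TG-APP vs WLC belongs to both H1a and H1b, so the same comparison could be read in two ways and give two answers.

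The second issue is precision. Randomisation makes the baseline means equal in expectation, but the model does not use this. The level contrast ignores baseline LSAS, and the change contrast subtracts it in full, which is more than a correlation below 1 warrants. What is at stake is precision in the comparison of TG-APP with APP, a central question of the trial and the one with the smallest planned effect.

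**Working it through.** **Inputs, all from Design and sample size unless noted**

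- Random-intercept and residual variances are 0.5 each, so the total is 1.0 and the baseline–post correlation is rho = 0.5/(0.5 + 0.5) = 0.5.
- APP effect: "we chose a conservative estimate of 30% post-treatment dropout for the APP condition and multiplied the expected effect size of 0.5 by 0.7", giving 0.35.
- TG-APP effect: "we expected a lower post-treatment dropout rate of 20% due to the additional guidance by a therapist and multiplied the expected effect size of 0.8"; the multiplier is 1 − 0.20 = 0.8, giving 0.64. TG-APP minus APP is 0.64 − 0.35 = 0.29.
- The target is that "the lower bound of the 95% confidence interval did not fall below 80% power, given" alpha 0.05. It was met at WLC 41, APP 61, TG-APP 61, with stated power 84% (80.0 to 87.0).
- Final arm sizes (Allocation and randomization): 43, 61, 61.

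**Step 1. Reproduce the stated power.** With two occasions and a random intercept, the interaction test is a test on change scores with variance 2 × 0.5 = 1.0. The noncentrality is Σn·d² − (Σn·d)²/N.

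- At 41/61/61: 61 × (0.35² + 0.64²) − (61 × 0.99)²/163 = 32.46 − 22.37 = 10.08.
- Power on 2 df is 81.9%; a simulation of the likelihood ratio test with 40,000 runs gave 81.8%.
- The protocol's 84% rests on 500 runs, with Monte Carlo standard error √(0.82 × 0.18/500) = 1.7 points. The recomputed value lies inside the stated interval, so the figure is reproduced within simulation error.

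**Step 2. Variance factor of each contrast** (multiplies 1/n₁ + 1/n₂):

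- difference in change: 2(1 − rho) = 1.00
- difference in post-treatment level: 1.00
- common baseline mean: 1 − rho² = 0.75

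Generalised least squares with the stated components confirms this. For TG-APP vs APP the variance is 2/61 = 0.0328 for both planned contrasts and 0.0246 with a common baseline mean. For APP vs WLC it is 1/61 + 1/43 = 0.0396, falling to 0.0297.

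**Step 3. Power at 43/61/61.** The noncentrality is 32.46 − (60.39)²/165 = 10.36, and 10.36/0.75 = 13.81. Pairwise power is Φ(d/SE − 1.96), two-sided 5%, without multiplicity adjustment.

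| Comparison | Effect | Planned | Common baseline mean |
|---|---|---|---|
| 2-df interaction | – | 83% | 92% |
| TG-APP vs WLC | 0.64 | 90% | 96% |
| APP vs WLC | 0.35 | 42% | 53% |
| TG-APP vs APP | 0.29 | 36% | 46% |

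For 80% power at 0.29, the number per arm falls from 187 to 140; 61 are planned.

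**Step 4. Sensitivity to rho.** The protocol gives no observed LSAS correlation, so 0.3 to 0.7 is an assumed range.

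| rho | Saving against change | Saving against level |
|---|---|---|
| 0.3 | 35% | 9% |
| 0.5 | 25% | 25% |
| 0.7 | 15% | 49% |

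**Step 5. How far the two planned contrasts can part.** With 61 per arm, a baseline difference of one standard error is √(2/61) = 0.18 SD. At rho = 0.5 it is expected to move the level contrast by 0.5 × 0.18 = 0.09 SD in one direction and the change contrast by 0.09 SD in the other. Each shift is about a third of 0.29 (0.09/0.29 = 0.31).

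**The case against.** The best defence is that the plan is valid as it stands. A group-by-time mixed model with free baseline means is standard. Both contrasts have the same expectation under randomisation, and chance imbalance is already in their standard errors. The powered test and the primary model agree, and the interaction test meets its target without any change. All of this stands.

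A reader might go further and infer that the plan is biased by baseline imbalance. The documents do not support that. The 0.09 SD shift is conditional on one realised imbalance and averages to zero over randomisations. Nor do they support the inference that the sample size is wrong, since Step 1 reproduces it for the test it was set for.

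It is also fair to say that rho = 0.5 is a simulation setting and that the equal 25% for both contrasts holds only there. At rho = 0.3 the gain over the level contrast is just 9%. The gain is nevertheless positive against both contrasts across the whole assumed range.

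Finally, an article may leave detail to an analysis plan. Here, though, the article itself states the model, the reading of its effects and the contrast for H1b, so these are choices already made.

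**Conclusion.** The point holds as a mismatch between hypothesis and contrast together with a loss of efficiency. It is a recommended improvement and not a flaw that invalidates the analysis. At the protocol's variance components, the planned contrasts forgo all of the variance reduction that baseline LSAS offers, which amounts to about 25% of the contrast variance. The 25% is not a share of the available reduction, which is lost entirely.

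The power figures treat data completed by jump-to-reference imputation as complete with diluted effects, as the protocol does; the actual variance under that imputation would differ. A reader might expect the change to cure the low pairwise power. It does not: APP vs WLC reaches about 53% and TG-APP vs APP about 46%, both well below 80%.

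**What to change.** Fit the primary model as a constrained longitudinal mixed model: one common baseline mean for the three arms, with arm effects at post-treatment and follow-up. Take the H1a and H1b contrasts from it at post-treatment. Keeping the longitudinal form also retains the model that H1c needs for post-treatment against follow-up, which a regression of post-treatment LSAS on baseline alone would not provide.

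Use the same form for secondary outcomes that have a baseline measurement. CGI-Improvement is excluded, because it rates change directly and has no baseline level.

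Reconcile the Objectives, Primary analysis and Secondary analyses sections so that H1a and H1b name the same contrast. This is needed even if the model is left as it is.

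The cost is a small change to the model code and a few sentences of protocol text, with no added participants, visits or data.

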### Procedure

The study will be conducted in Germany at the outpatient psychotherapy unit of the Clinical Psychology department of the Goethe University of Frankfurt as well as the outpatient psychotherapy unit of the Clinical Psychology department of the Technische Universitaet Dresden and two further CBT training centers in Dresden. For reporting purposes, we followed the SPIRIT reporting guidelines [27].

In the first step, all persons that register for participating in the study will be screened using an online self-report assessment. If participants exceed the cut-off of 25-points or find themselves within the criteria for social anxiety disorder, they are referred to another online self-assessment and then invited for an interview with a clinical rater. Beforehand, they will be informed about the study and provided with written informed consent (either personally or via email if necessary). Interviews to determine the patient's formal diagnosis are conducted by blinded and independent psychologists (with at least a master’s degree) who have been trained in the appropriate interviews. Eligible patients are then randomly assigned to one of three groups (WLC, APP, TG-APP). Participation in each of the groups lasts 3 months. Participants in the WLC group then have the option of using the app if they wish. The outcome measures will be assessed by blinded and independent raters at baseline, post-treatment (3 months after start), as well as 6 months after the post-treatment interview (follow-up). Furthermore, participants will complete self-report questionnaires online at baseline, at mid-treatment (at 6 weeks), post-treatment (at 12 weeks), and follow-up (at 36 weeks; see Fig. 1 for the study flowchart). Interviewers will remind patients to fill out the self-report questionnaires and if necessary, patients will be contacted by the study coordinator to complete the missing questionnaires.

Prior to the start of the study, we will conduct a pilot study to improve usability and evaluate the mobile application and the applicability of therapist-guided video therapy and the videoconferencing tool.

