Clark and Wells’ model [4] aims to change the factors that maintain social anxiety. Treatment includes derivation of a model and behavioral experiments to test the effect of safety behaviors and self-focused attention, attention training, video feedback, further behavioral experiments, and cognitive restructuring. Based on this model and its German adaptations by Stangier et al. [28] and Hoyer and Härtling [29], the treatment includes the following modules:Module 1—Learning and Understanding: The goal of this module of the app is to provide the user with key information about SAD and to create an individualized model based on Clark and Wells’ approach. The information used to derive the model is based on patients’ self-reports of anxiety-provoking situations. The model is developed in a stepwise manner, prompted by feedback from the app.Module 2—Attention Training: The goal of the second module is to change self-focused attention. The training uses recorded audio exercises that train the ability to focus attention on external stimuli.Module 3—Behavioral experiments: This key module of the app consists of four phases. Each phase includes specific types of behavioral experiments, as well as various forms and questions for planning the experiments and recording the results and key findings.The first phase provides an experiment on how increasing or decreasing safety behaviors and self-focused attention affects anxiety. The experiment is supplemented by video feedback, in which patients are asked to record themselves in a simulated social situation (e.g., a presentation) and subsequently correct dysfunctional beliefs about their appearance or behavior.The second phase involves testing the dysfunctional beliefs that emerge in real social situations while simultaneously reducing safety behaviors and directing their attention outward.The third phase focuses on testing beliefs about the assumed negative impact of supposedly embarrassing behaviors on how they are evaluated by others (e.g., “If I pause during a presentation, I will appear awkward, and others will think I am an idiot”). Patients are instructed to explicitly demonstrate certain critical behaviors (e.g., pausing during a presentation) and to question the validity of their (possibly erroneous) beliefs.The fourth phase involves integrating behavioral experiments into daily life by continually testing SAD-related beliefs that interfere with personal goals.

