### Statistical methods

#### Sample

All analyses will be conducted in the intent-to-treat (ITT) sample, including all participants that were randomized into one of the three groups.

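### The only model described for the secondary outcomes adjusts for app-use time and number of behavioural experiments, both of which follow randomisation, so its between-arm contrasts at a given time are not intention-to-treat effects

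*Protocol article*

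**What the plan says.** In the Protocol article, the section Secondary analyses sets the purpose: "we will evaluate treatment effects (from baseline to post-treatment, as described in hypothesis 2a" and, for hypothesis 2c, from post-treatment to follow-up. Hypothesis 2b (Objectives) states that under TG-APP "improvements in secondary outcome variables from baseline to post-treatment will be significantly larger than in the APP condition".

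The model for these outcomes comes at the end of the same section: "We will fit all measures as outcome variables in linear mixed models including the same predictors as in the primary analysis". The sentence goes on to "add the average weekly time participants spent using the app and the number of behavioral experiments conducted as additional explanatory predictors". No fit without these two variables is described for the secondary outcomes, and no interaction of either with time or arm is specified.

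Two other statements frame the choice. Under Sample: "All analyses will be conducted in the intent-to-treat (ITT) sample, including all participants that were randomized into one of the three groups". In Procedure, after the three-month period: "Participants in the WLC group then have the option of using the app if they wish".

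For comparisons between two arms at a given time, Secondary analyses plans emmeans contrasts and cites hypotheses 1b and 2b, although the sentence names only LSAS differences. The LSAS model under Primary analysis has time, arm and their interaction, and neither engagement variable.

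**The concern.** App-use time and number of experiments are consequences of the assigned arm. WLC has no app until the three months are over. Behavioural experiments belong to the treatment itself; of the module that holds them the section Treatment says: "This key module of the app consists of four phases". The Discussion gives better use of such experiments as a reason why therapist guidance should add benefit.

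A model that holds these variables fixed asks how the arms would differ at equal use. That is a different question from hypotheses 2a and 2b, which compare the arms as randomised. For WLC it also extrapolates to a level of use that the arm could not have. For hypothesis 2b it conditions on the mechanism by which TG-APP is supposed to surpass APP. At stake is the meaning of the secondary efficacy results: quality of life, depression, distress, impairment, social-phobic cognitions and interpersonal pleasure.

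**Working it through.** The article states no figure for the secondary models, so there is none to reproduce. The size below is illustrative and borrows the planning values for the LSAS.

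**Inputs from the Protocol article**
- Arm sizes: WLC 43, APP 61, TG-APP 61 (Allocation and randomization).
- Random-intercept variance 0.5 and residual variance 0.5 (Design and sample size).
- Effects against WLC after the dropout reduction: 0.5 × 0.7 = 0.35 for APP and 0.8 × 0.8 = 0.64 for TG-APP. The difference is 0.29 (Design and sample size).

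**Assumptions, not in the article**
- m is the share of the effect that runs through use, taken as 0.5 or 1.
- Where use in minutes is needed: means 0, 30 and 45 in WLC, APP and TG-APP, with SD 15.

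Improvement is counted as positive, and δ is the true arm difference in improvement.

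**Step 1. Covariates as time-constant main effects (the literal reading), baseline and post-treatment, complete data.** A random-intercept model then splits into a regression of each person's change and a regression of each person's mean.
- Change: a time-constant covariate drops out, so the group-by-time contrast stays at δ.
- Mean: only the post value carries the effect, so the use-adjusted arm contrast is δ(1 − m)/2.
- Post-treatment contrast = mean contrast + half the change contrast = δ(1 − m)/2 + δ/2 = δ(1 − m/2).
- Baseline contrast = δ(1 − m)/2 − δ/2 = −mδ/2, a difference that randomisation did not create.

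| Contrast | Group × time | Post, m = 0.5 | Post, m = 1 | Baseline, m = 1 |
|---|---|---|---|---|
| APP − WLC | 0.35 | 0.26 | 0.18 | −0.18 |
| TG-APP − WLC | 0.64 | 0.48 | 0.32 | −0.32 |
| TG-APP − APP | 0.29 | 0.22 | 0.15 | −0.15 |

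Check: with full mediation through use of 0/30/45 minutes and effects 0.50, 0.75 and 0.25, the formula gives 0.25, 0.375 and 0.125. A simulation of 2,000 trials gave 0.247, 0.366 and 0.119. A smaller simulation with both covariates (80 trials per scenario, so noisier) gave TG-APP versus WLC as 0.60 falling to 0.41 at m = 0.5, and 0.65 falling to 0.18 at m = 1. With dropout added, the group-by-time estimates differed from the unadjusted ones by at most 0.002.

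**Step 2. Covariates time-varying or interacting with time.** Change is now regressed on arm and use. The adjusted contrast is δ − λΔU, where ΔU is the arm difference in mean use and λ the within-arm slope of improvement on use.
- No confounding: λΔU = mδ, so the contrast is δ(1 − m). For APP and TG-APP against WLC that is 0.18 and 0.32 at m = 0.5, and 0 and 0 at m = 1.
- Confounding of c SD of outcome per SD of use: λΔU = mδ + c × ΔU/SD. For APP versus WLC with m = 0.5 and ΔU/SD = 30/15 = 2:
  - c = +0.3: 0.35 − (0.175 + 0.6) = −0.425, a reversed sign.
  - c = −0.3: 0.35 − (0.175 − 0.6) = 0.775, an inflated effect.

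The 80-trial simulations, with other assumed use distributions, showed the same pattern for APP/TG-APP versus WLC: −0.36/−0.65 for c = +0.3 and 0.64/1.21 for c = −0.3.

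**Step 3. Precision.** The variance of a change is 2 × 0.5 = 1.0, so the unadjusted standard error against WLC is √(1/43 + 1/61) = 0.20. In the two-covariate simulations the spread of the contrasts that the covariates affect rose to 0.3–0.6 in most scenarios.

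**The case against.** The strongest reply is that hypotheses 2a and 2b concern improvement from baseline to post-treatment, which is the group-by-time contrast. The two variables read as one summary per person with no time interaction, and Step 1 shows that this contrast is then untouched with complete data. That stands. It limits the point to contrasts at a given time, unless the covariates are coded to act over time.

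Second, the emmeans sentence speaks of LSAS, whose primary model has neither covariate. This stands in part: the sentence also cites hypothesis 2b, which is about the secondary outcomes, and the only model described for those outcomes is the adjusted one.

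Third, the engagement variables may have been meant for an extra, explanatory model, with details left to an analysis plan. The sentence does not say so. It fixes a single model for all measures and labels nothing exploratory.

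Three stronger inferences are tempting, and the documents do not support them:
- *The secondary effects are biased toward zero, so an effective arm will look ineffective.* Step 2 shows attenuation, reversal or inflation, depending on how engagement and outcome are confounded. The near-zero results need full mediation and a time-acting covariate, neither of which the article states.
- *Group-by-time may be pruned from these models.* The instruction to "remove all non-significant interactions from the final model" closes the paragraph on hypotheses 3 and 4 and is not invoked for the secondary-outcome models. If it did reach group-by-time, simulation puts removal at 17% of trials at the planning effects and 71% at half those effects. Retained estimates at the planning effects would be inflated, to 0.38 and 0.70. A clarifying clause is enough.
- *WLC has no app use at any assessment.* That holds only to post-treatment, since WLC may use the app afterwards.

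**Conclusion.** The point holds in limited form and should be fixed. The one model described for the secondary outcomes conditions on two consequences of treatment. Its arm contrasts at a given time are not the intention-to-treat effects that hypotheses 2a and 2b and the Sample section call for. If the covariates act over time, neither are its change contrasts.

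The size cannot be fixed from the article. On the literal coding without confounding, the time-point contrast loses half of whatever share runs through use: a quarter of the effect at m = 0.5 and half at m = 1. The change contrast loses nothing with complete data. With time-acting covariates the loss equals the mediated share, and confounding can move the result either way. Attenuation is plausible because use is the intended mechanism, but it is not assured. All these figures rest on assumed use distributions and mediated shares. The primary LSAS analysis is unaffected, so the trial's main conclusion does not depend on this.

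**What to change.** In Secondary analyses:
1. State that hypotheses 2a to 2c are tested for every secondary outcome with the primary-analysis predictors only (group, time, group × time), and that contrasts at a given time come from that fit.
2. Move average weekly app time and number of behavioural experiments to a separate model restricted to APP and TG-APP, labelled exploratory and non-causal.
3. As a minor clarification, say that removal of non-significant interactions applies only to the moderator and mediator terms for hypotheses 3 and 4, and that group × time always stays in the model.

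The cost is a few sentences of protocol wording and one extra exploratory model. No additional data or participants are needed, and the change should be made before the data are analysed.
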